- At each update of the distribution (interim analysis), a stopping rule for efficacy will recommend stopping the trial if there is a high predictive probability ( $\geq 80\%$ ) that the ORR (for cohorts A as well

as C to G) or 6-month PFR (for cohort B) is higher or equal to the the maximal response probability threshold  $p_1$  (Strata A and E:  $p_1=20\%$ ; Strata B/C/D/F:  $p_1=40\%$ ; Stratum G:  $p_1=25\%$ ).

- The trial will continue until the stopping rule applied at each interim analysis is met, or until the maximum sample size of 50 patients is reached.
- When a trial is not completed to allow efficacy analysis, descriptive data only are presented.

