#### **10.1.3. Phase II trial: Cohort H (NSCLC)**

- We rely on a single-arm phase 2 trial based on an optimal two-stage Simon's design [91].
- Treatment will be considered promising if 6-month PFR ( $\geq 20\%$ ).
- Hypotheses are the following [62] :
  - 20% 6-month PFR (null hypothesis),
  - 40% acceptable 6-month PFR (alternative hypothesis),
  - 5% 1-sided type I error rate,
  - 80% power,
- A total of 43 eligible and assessable subjects will be necessary, with 13 assessable subjects recruited to the first stage.
- Stage 1: Following the inclusion of the first 13 assessable patients, if 3 or less patients are progression-free at 6 months (complete response, partial response or stable disease), the study will be terminated early. Otherwise, if 4 or more patients are progression-free at 6 months, the second group of subjects will be recruited.
- Stage 2: If at the end of recruitment, 13 patients or more are progression-free at 6 months (out of the 43 eligible and evaluable patients), treatment will be considered worthy of further testing in this disease (efficacy rate  $\geq 20\%$ ).
- Inclusions will not be suspended after the recruitment of the first 13 patients while data are being analysed for the first stage of inclusion.
- In order to account for not evaluable patients (+/- 10%), 47 patients will be recruited.

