##### 10.3.2.2. PHASE II TRIALS

- All analyses will be descriptive; no p-values will be calculated.
- Analyses will be conducted independently for each phase II trial.
- Analysis of the primary efficacy endpoint will be analysed based on the eligible population assessable for efficacy (see chapter 10.2 for definition):
  - Each patient will be assigned one of the following categories:
    - Confirmed complete response (CR)
    - Unconfirmed complete response (CRu)
    - Confirmed Partial response (PR)
    - Unconfirmed Partial response (PRu)
    - Stable disease
    - Progression (Clinical PD and radiological PD will be reported separately)

- Inevaluable for response
- Depending on the cohort, the rate of objective response (ORR: CR, CRu, PR, PRu) under treatment or the progression-free rate (PFR: CR, CRu, PR, PRu, SD) will be reported:
  - All eligible and assessable patients (section 10.2) will be included in the denominator for the calculation of the ORR/PFR.
  - The 95% two-sided confidence limits will be provided for the ORR/PFR (binomial law).
  - First endpoint conclusions will be based on the ORR/PFR for all eligible and assessable patients (section 10.2) after centralized radiological review of the data.
- As regards to the other efficacy endpoints, the analyses will be carried out in the eligible and assessable population:
  - Each patient will be assigned one of the following categories:
    - Confirmed complete response (CR)
    - Unconfirmed complete response (CRu)
    - Confirmed Partial response (PR)
    - Unconfirmed Partial response (PRu)
    - Stable disease
    - Progression
    - Inevaluable for response
  - The rate of best overall response will be calculated as the number of patients alive with the best response (recorded from the start of the treatment) divided by the number of patients eligible and assessable (section 10.2).
  - The 6-month progression-free rate will be calculated as the number of patients remaining alive and progression-free at 6 months from the start of the treatment divided by the number of patients eligible and assessable (section 10.2).
  - The 6-month objective response rate will be calculated as the number of patients alive with complete or partial response at 6 months divided by the number of patients eligible and assessable (section 10.2).
  - The 95% two-sided confidence limits will be provided for the calculated rates (binomial law)
- The safety analysis will be performed on the safety population.

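### Section 10.3.2.2 gives raw rates with single-stage two-sided 95% binomial limits to every phase II cohort, which does not match the cohorts that can stop early or the one-sided 5% decisions

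*Protocol*

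**What the plan says.** Protocol section 10.3.2.2 sets one reporting rule for the phase II primary endpoint.

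- Denominator: "All eligible and assessable patients (section 10.2) will be included in the denominator for the calculation of the ORR/PFR".
- Interval: "The 95% two-sided confidence limits will be provided for the ORR/PFR (binomial law".
- Role: "First endpoint conclusions will be based on the ORR/PFR for all eligible and assessable patients (section 10.2".

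The section calls all analyses descriptive, without p-values. It also uses binomial limits for qualitative variables in general. I take that to cover the disease control rate of cohorts J to L, which the ORR/PFR sentence does not name.

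The designs behind this rule differ.

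- **A to G (10.1.2):** looks after 10 patients and then every 5, up to 50, with a Beta(1,1) prior. There is a futility rule, and "a stopping rule for efficacy will recommend stopping the trial" at an 80% probability. Inclusions normally go on between looks. The success probability is said to come from a beta-binomial model, but 10.3.2.2 does not carry this into the reported figures.
- **H (10.1.3):** "We rely on a single-arm phase 2 trial based on an optimal two-stage Simon's design", with "20% 6-month PFR (null hypothesis", "40% acceptable 6-month PFR (alternative hypothesis" and "5% 1-sided type I error rate". The cohort stops at 3 or fewer of 13 and succeeds at 13 or more of 43. A' (10.1.5) has the same numbers for 4-month PFR.
- **I (10.1.4):** null 15%, alternative 40%. It stops at 2 or fewer of 13 and succeeds at 8 or more of 29.
- **J to P (10.1.6 to 10.1.10):** one stage, one-sided 5%.

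**The concern.** A raw proportion is unbiased, and single-stage binomial limits have the right reference distribution, only when the sample size does not depend on the results. That is true of J to P. In A to G an efficacy stop needs a high count, so stopping selects high estimates. In H, I and A' a futility stop freezes low estimates at a small sample size.

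Separately, a two-sided 95% interval tests at one-sided 2.5%, while H, I, A' and J to P decide at one-sided 5%. A cohort can then be declared successful beside an interval that includes the null.

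Because no p-values are planned, the rate and its interval are the published result. They are what planners of the next trial would use.

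**Working it through.** **1. The plan's own Simon figures.** For H and A', P(success | p) = Σ over x = 4 to 13 of b(x; 13, p) · P(Y ≥ 13 − x), with Y ~ Bin(30, p). This gives 0.0496 at p = 0.20 and 0.800 at p = 0.40. The same sum for I (continue from x = 3, succeed at 8 of 29) gives 0.0500 at 0.15 and 0.907 at 0.40. Both designs reproduce.

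**2. Mean raw rate in the Simon cohorts.** E = Σ over x ≤ r1 of b(x)·x/13 + Σ over x > r1 and all y of b(x)·b(y)·(x + y)/n.

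- H at 20%: 17.4%. H at 40%: 37.6%.
- I at 15%: 12.9%. I at 40%: 39.2%.

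The bias is downward in each case. These means count a futility-stopped cohort at 13 patients. Inclusions are not suspended during the stage 1 analysis, so the bias would be smaller if later patients entered the rate.

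At the success boundary the uniformly minimum-variance unbiased estimate (UMVUE) lies above the raw rate: 37.1% against 30.2% at 13/43, and 30.7% against 27.6% at 8/29.

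**3. Lower limits at the lowest successful counts.** Single-stage limits are Clopper-Pearson. The stage-wise lower limit is the p at which the two-stage probability of a result at least as high equals 2.5% (95% limits) or 5% (90% limits).

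| Result | Null | Single-stage 95% | Single-stage 90% | Stage-wise 95% | Stage-wise 90% |
|---|---|---|---|---|---|
| 13/43 | 20% | 17.2% | 18.9% | 18.2% | 20.0% |
| 14/43 | 20% | 19.1% | 20.9% | 19.8% | 21.7% |
| 8/29 | 15% | 12.7% | 14.5% | 13.1% | 15.0% |

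The full single-stage 95% intervals are 17.2–46.1%, 19.1–48.5% and 12.7–47.2%. The stage-wise 90% limits are 20.0–50.0% at 13/43 (one-sided p = 0.0496) and 15.0–45.8% at 8/29 (p = 0.04999). At the exact boundary, neither the stage-wise ordering nor the 90% level is enough alone; both are needed. From 15/43 (21.0%) and 9/29 (15.3%) on, the single-stage 95% interval clears the null.

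In J to P the level alone causes the same overlap:

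| Result | Null | 95% lower | 90% lower |
|---|---|---|---|
| 8/28 | 15% | 13.2% | 15.1% |
| 8/40 | 10% | 9.1% | 10.4% |
| 12/35 | 20% | 19.1% | 21.1% |

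**4. A to G after an efficacy stop.** Assumption: the 80% predictive probability is read as a posterior probability, because the protocol gives no predictive horizon. With s successes in n, the posterior is Beta(1 + s, 1 + n − s), and the cohort stops if P(rate ≥ p1) ≥ 0.80. In A/E, 3/10 gives 0.839 and stops; 2/10 gives 0.617 and continues. A cohort stopped at its first look therefore shows at least 30% at that look, and that look supplies 0.32 of the 0.50 stopping probability when the truth is 20%.

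If m further patients enter the denominator (capped at 50), the expected rate becomes (s + m·p)/(n + m). For example, 3/10 followed by 10 patients at 20% gives (3 + 2)/20 = 25%. The protocol gives no accrual rate, so m = 0, 10 and 20 show a range. Exact enumeration with truth = p1:

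| Cohorts | True rate | P(efficacy stop before 50) | Mean, m = 0 | m = 10 | m = 20 |
|---|---|---|---|---|---|
| A/E | 0.20 | 0.50 | 0.326 | 0.269 | 0.250 |
| B/C/D/F | 0.40 | 0.43 | 0.563 | 0.493 | 0.468 |
| G | 0.25 | 0.47 | 0.391 | 0.328 | 0.306 |

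Averaged over all outcomes, the bias is about +4.6 points at m = 0, +1.8 at m = 10 and +0.7 at m = 20. At m = 0 the flat-prior posterior mean does not remove it: it averages 26.3%, 44.6% and 30.8%.

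**5. Coverage (m = 0).** Averaged over all outcomes, the binomial interval covers about 95% or more in every scenario computed (lowest 94.97%, G at 25%). It fails after an efficacy stop when the truth is p0: every such interval then excludes the true rate. That event has probability 1.2% (A/E), 1.0% (B/C/D/F) and 2.0% (G).

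**The case against.** The strongest reply is that the large A to G figures describe a cohort frozen at the look that triggers the stop. Section 10.1.2 keeps inclusions open between looks, waits for 16 weeks of follow-up and only recommends stopping, and all assessable patients enter the denominator. This stands: the excess shrinks considerably with 10 or 20 further patients, though its direction does not reverse. The excess is also smaller if the drug does better than p1. Ten points above p1, with no added patients, the mean after an efficacy stop is 0.360, 0.585 and 0.420 against 0.30, 0.50 and 0.35.

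The go/no-go decision also does not use the interval. H, I and A' decide on counts, A to G on the Bayesian rule, and the analyses are labelled descriptive. This stands too, and it limits the point to reporting and interpretation.

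Finally, an analysis plan could add adjusted estimates. It could, but this is not a detail that the protocol leaves open: section 10.3.2.2 names the method.

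A reader might infer that every cohort able to stop early will report too high a rate. The documents do not support that: H, I and A' have no efficacy stop, and their raw rates are biased downward overall. A reader might also blame the Simon overlap on single-stage limits alone. The two-sided 95% level contributes as well, and the single-stage cohorts J to P share that part.

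**Conclusion.** The point holds as a mismatch between the stated estimator and interval and the designs they serve.

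- **A to G:** the raw rate after an efficacy stop is too high on average when the truth is p1. The excess is about 13 to 16 points with no added patients, 7 to 9 with 10, and 5 to 7 with 20. The size rests on the posterior reading of the rule and on accrual, which the protocol does not give; the direction holds in every case computed.
- **H, I and A':** the raw rate is biased downward overall. The interval disagrees with a declared success only at 13–14 of 43 and 8 of 29.
- **J to P:** the binomial method is right. Only the level disagrees with the one-sided 5% test at the success boundary.

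It would be wrong to conclude that the binomial limits are generally invalid or that any cohort decision is unsafe: overall coverage is about 95% or higher and no decision changes. This is a worthwhile, low-cost improvement, not a design fault.

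**What to change.** Amend section 10.3.2.2. Keep the raw proportion and its binomial limits, and add beside them:

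- **H, I and A':** a UMVUE or median-unbiased estimate with stage-wise two-sided 90% limits, computed from the stage sizes actually reached. At the planned sizes the lower limits are 20.0% at 13/43 and 15.0% at 8/29, in agreement with the decision.
- **A to G:** a bias-adjusted estimate and an interval based on the looks actually taken and the patients accrued after the stop.
- **J to P:** the two-sided 90% binomial limits that match the one-sided 5% test.

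The cost is a few sentences and slightly more analysis with standard methods. Design, sample size and patient care are unchanged. Reported rates in A to G become less favourable after an efficacy stop; at the Simon success boundary the adjusted rate is higher than the raw one.

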#### **10.1.6. Phase II trial : Cohorts J (Urothelial cancer) and L (Triple negative breast cancer)**

- We rely on a single-arm phase 2 trial based on an exact single stage design (A'Hern).
- Treatment will be considered promising if 6-month DCR  $\geq 15\%$ .
- Hypotheses are the following:
  - 15% 6-month DCR (null hypothesis),
  - 35% 6-month DCR (alternative hypothesis),
  - 5% 1-sided type I error rate,
  - 80% power,
- A total of 28 eligible and assessable subjects will be necessary. If at the end of recruitment, 8 patients or more have disease control at 6 months (out of the 28 eligible and evaluable patients), treatment will be considered worthy of further testing in this disease (efficacy rate  $\geq 15\%$ ).
- In order to account for not evaluable patients (+/- 10%), 31 patients will be recruited.

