#### Rules of decision for patient's replacement:

- Any patient not eligible or not assessable for efficacy will be replaced.
- However, any patient who received at least one administration of the study drug will be included in the safety analysis.

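### In cohorts H, I, A' and J to P the success count is set for a fixed number of assessable patients, but the conclusion is drawn on all of them, so any shortfall in the expected 10% loss can take the type I error above 5%

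*Protocol*

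**What the plan says.** Each Simon or A'Hern cohort has a success rule that is a whole number of patients out of one named denominator. For cohort H (section 10.1.3) it is "13 patients or more are progression-free at 6 months (out of the 43 eligible and evaluable patients"), derived from "20% 6-month PFR (null hypothesis") against "40% acceptable 6-month PFR (alternative hypothesis") with a "5% 1-sided type I error rate". For cohorts J and L (section 10.1.6) it is "8 patients or more have disease control at 6 months (out of the 28 eligible and evaluable patients"). The other sections from 10.1.4 to 10.1.10 have the same form.

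The same sections then recruit more than that number. For J and L: "In order to account for not evaluable patients (+/- 10%), 31 patients will be recruited". The corresponding figures are 47 for H and A', 32 for I, 31 for N, 44 for K and P, and 39 for M and O.

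Section 10.2.2 adds a replacement rule: "Any patient not eligible or not assessable for efficacy will be replaced". Section 10.3.2.2 puts every eligible and assessable patient in the denominator and states: "First endpoint conclusions will be based on the ORR/PFR for all eligible and assessable patients". That sentence names ORR and PFR only. Cohorts J, K and L, whose endpoint is 6-month DCR, are reached through the more general statement in the same section that the primary efficacy endpoint is analysed in the eligible population assessable for efficacy.

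**The concern.** A success count holds its type I error only at the number of patients for which it was derived. With more patients and the same count, success becomes easier under the null. The protocol names two decision sets, the design number in 10.1 and all assessable patients in 10.3.2.2. They coincide only if exactly the design number turns out assessable. When more are assessable, nothing says whether the late patients count or whether the cut-off moves.

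These are uncontrolled cohorts, and whether the treatment is judged worth further testing rests on this one integer. If the choice of set is left open, the same data could be called positive or negative, and the choice could be made after the results are known.

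**Working it through.** **Inputs** (sections 10.1.3 to 10.1.10)

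| Cohorts | p0 / p1 | Stage 1 | Success count c | Design n | Recruited N |
|---|---|---|---|---|---|
| H, A' | 20% / 40% | continue if 4 or more of 13 | 13 | 43 | 47 |
| I | 15% / 40% | continue if 3 or more of 13 | 8 | 29 | 32 |
| J, L, N | 15% / 35% | none | 8 | 28 | 31 |
| K, P | 10% / 25% | none | 8 | 40 | 44 |
| M, O | 20% / 40% | none | 12 | 35 | 39 |

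All state 5% one-sided error. Power is 80%, or 90% for cohort I.

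**Formulas**

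- Single stage: alpha(n) = P(X ≥ c), with X ~ Bin(n, p0).
- Two stage: alpha(n) = Σ P(X1 = x) · P(X2 ≥ c − x), summed over x from the continuation bound to 13, with X1 ~ Bin(13, p0) and X2 ~ Bin(n − 13, p0).
- Power: the same expressions with p1 in place of p0.

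**Step 1. The plan's own designs at the design n**

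- H, A': alpha 4.96%, power 80.0%
- I: alpha 5.00%, power 90.7%
- J, L, N: alpha 4.86%, power 81.8%
- K, P: alpha 4.19%, power 81.8%
- M, O: alpha 3.44%, power 80.5%

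All reproduce. The two-stage designs are the Simon optimal ones, and the single-stage designs are the smallest that meet 5% and 80%.

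**Step 2. Same count and same stage 1 rule, more assessable patients**

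| Cohorts | design n | +1 | +2 | +3 | +4 |
|---|---|---|---|---|---|
| H, A' (43 to 47) | 4.96% | 5.62% | 6.31% | 7.02% | 7.76% |
| I (29 to 32) | 5.00% | 5.79% | 6.63% | 7.50% | – |
| J, L, N (28 to 31) | 4.86% | 5.86% | 6.98% | 8.22% | – |
| K, P (40 to 44) | 4.19% | 4.77% | 5.39% | 6.07% | 6.79% |
| M, O (35 to 39) | 3.44% | 4.24% | 5.17% | 6.23% | 7.42% |

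The last entry in each row is the case in which every recruited patient is assessable.

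**Step 3. How likely a surplus is**

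This is an illustration under an assumption. Suppose each recruited patient is independently assessable with probability 90%, the plan's own allowance, and a two-stage cohort goes on to full recruitment. Then P(Bin(N, 0.9) > n) is 30% for H and A', 37% for I, 39% for J, L and N, 35% for K and P, and 44% for M and O.

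In K, P, M and O it takes two surplus patients to pass 5%, that is, at most two losses. For K and P this is 0.9^44 + 44(0.1)(0.9^43) + 946(0.01)(0.9^42) = 17%. For M and O it is 0.9^39 + 39(0.1)(0.9^38) + 741(0.01)(0.9^37) = 24%.

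At 95% assessable, the chance of any surplus is 79% to 87% across the cohorts.

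**Step 4. Whether replacement adds patients beyond the 10%**

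Seven Bayesian cohorts of 50, plus the recruited numbers above, give 7×50 + (47 + 32 + 47) + 3×31 + 2×44 + 2×39 = 350 + 126 + 93 + 88 + 78 = 735. This is the phase II total in the synopsis, so it holds no further allowance for replacement.

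**The case against.** The strongest answer is that every rule in 10.1 names its denominator, and no sentence applies 13 to 47 patients or 8 to 31. Section 10.3.2.2 is general text for all 17 cohorts. It fixes the population, keeps inevaluable patients in the denominator and gives central review the final word, but contains no count. At the planned 10% loss the assessable number is close to the design number and the two sets agree. The analyses are called descriptive, without p-values, and a statistical analysis plan is promised before the first phase II analysis.

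Much of this stands. The protocol does not prescribe the inflated rule; it leaves two readings open. However, 10.3.2.2 does not only define a reported rate: it says on whom the conclusion is based, and it says all. The counts, the over-recruitment and the decision population are all fixed in this document, so the conflict lies within it. Leaving out p-values does not remove a binding count with a stated 5% error.

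A reader might also infer that the 10% over-recruitment and the replacement rule add together and push the assessable number higher still. The total of 735 does not support that. The 10% is already the replacement allowance, and a surplus arises only when losses fall short of it.

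**Conclusion.** The concern holds in a limited form. If the stated count is applied to all assessable patients and there are more of them than the design number, the stated 5% is exceeded: with one surplus patient in H, A', I, J, L and N (5.6% to 5.9%), and with two in K, P, M and O (5.2% to 5.4%). The figures of 6.8% to 8.2% are upper bounds that need every recruited patient to be assessable. With exactly the design number there is no inflation.

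A reader might take these figures to mean that the 5% is lost in all ten cohorts, or that 7% to 8% is to be expected. Neither follows: K and P (4.8%) and M and O (4.2%) stay below 5% with one surplus patient, and the upper bounds contradict the plan's own assumption of 10% loss. Still, a surplus is an ordinary outcome, with a chance of about 30% to 44% under that same assumption, so the decision set should be fixed before results are seen.

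**What to change.** In section 10.3.2.2, state that for cohorts H, I, A' and J to P the go/no-go rule (on PFR or DCR, as the cohort requires) is applied to the first 43 (H), 29 (I), 43 (A'), 28 (J, L, N), 40 (K, P) or 35 (M, O) eligible and assessable patients in order of inclusion. Report the rate and its 95% confidence interval in all assessable patients as supportive. Naming DCR there also closes the gap for J, K and L.

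This keeps the designed error of 3.4% to 5.0% and power of 80% to 91%. It needs no extra patients. The small cost is that a few late patients do not enter the formal decision. If that is unwelcome, the alternative is to give the cut-off for each attainable number in advance; with all recruited patients assessable it would be 14 of 47, 9 of 32, 9 of 31, 9 of 44 or 13 of 39.

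A sentence in 10.2.2 saying that the 10% is the replacement allowance would be a useful clarification and no more, since the planned total already implies it.

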## **9.2. PHASE II TRIALS**

### **9.2.1.Primary endpoint**

- Primary objective is to investigate the antitumor activity of Regorafenib when prescribed in association with Avelumab, independently for 17 cohorts of patients : Colorectal cancer not MSI-H or MMR-deficient (cohorts A and A' with immune signature (based on low tumor-associated macrophages infiltrate level), GIST (Cohort B), Oesophageal or gastric carcinoma (cohort C), Biliary tract cancer, hepatocellular carcinoma (Cohort D), Soft Tissue Sarcoma (STS – Cohort E), Radioiodine-Refractory Differentiated Thyroid Cancer (RR-DTC – Cohort F), Neuroendocrine gastroenteropancreatic tumors (GEP-NETs – Cohort G), Non-small cell lung cancer (Cohort H), Solid tumors (including Soft Tissue Sarcoma) with immune signature (TLS+) (Cohort I), urothelial cancer (Cohort J), HPV-associated cancer (Cohort K), triple negative breast cancer (L), TMB-high solid tumors (Cohort M), MSI-high solid tumors (Cohort N), non clear-cell renal carcinoma (Cohort O) and malignant pleural mesothelioma (Cohort P).
- For cohorts A, as well as C to G, antitumor activity will be assessed in terms of objective response under treatment based on adapted RECIST 1.1 criteria, and after in-stream centralized radiological review:

- Objective response under treatment is defined as patients with confirmed complete response (CR) or partial response, as per RECIST v1.1 criteria, observed during treatment with the investigational product(s).
- As per RECIST v1.1 criteria, to be considered as “confirmed”, complete and partial responses will have to be confirmed at least 4 weeks later to ensure responses identified are not the result of measurement errors. If the new imaging to confirm response is not performed after 4 weeks, complete or partial responses will be considered as unconfirmed responses.
- Objective response rate (ORR) under treatment is defined as the proportion of patients with objective response (confirmed or unconfirmed) under treatment based on adapted RECIST 1.1 (taking into account “unconfirmed “responses).

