### **9.2.2.Secondary endpoints**

- Best overall response is defined as the best response across all time points (RECIST v1.1). Following RECIST v1.1 recommendations:
  - The best overall response is determined once all the data for the patient is known.
  - The best overall response will be classified as confirmed complete response (CR), unconfirmed complete response (CRu), confirmed partial response (PR), unconfirmed partial response (PRu), stable disease or progressive disease, as per RECIST v1.1 criteria.
  - As per RECIST v1.1 criteria, to be considered as “confirmed”, complete and partial responses will have to be confirmed at least 4 weeks later to ensure responses identified are not the result of measurement errors.
- Objective response rate at 6 months (6-month ORR) is defined as the proportion of patients with objective response (confirmed or unconfirmed) at 6 months.
- Progression-free status is defined as complete response (confirmed or unconfirmed), partial response (confirmed or unconfirmed) or stable disease more than 24 weeks as defined as per RECIST v1.1 criteria (appendix 3). 6-month progression-free rate (6-month PFR) is defined as the proportion of patients with progression-free status at 6 months. 4-month progression-free rate (4-month PFR) is defined as the proportion of patients with progression-free status at 4 months.
- Growth modulation index (GMI): GMI is defined for each patient as the ratio of its PFS on Regorafenib + Avelumab treatment to its PFS on the previous line of therapy. This method accounts for inter-patient variability, the patient serving as his/her own control and implies by the natural history of the disease that the PFS tends to become shorter in successive lines of therapy. It is thought that an anti-cancer agent should be considered effective if the GMI is greater than 1.3
- Progression-free survival (PFS) is defined as the time from study treatment initiation to the first occurrence of disease progression or death (of any cause), whichever occurs first. 1-year PFS rate and median PFS will be reported.

- Overall Survival (OS) is defined as the time from study treatment initiation to death (of any cause). 1-year OS rate and median OS will be reported.
- Safety profile of the association Regorafenib + Avelumab: Toxicity will be graded using the common toxicity criteria from the NCI v5.0.
- Pharmacodynamic activity:
  - archived tumor tissue will be collected for assessment of the tumor microenvironment.

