#### 10.1.2. Phase II trials: Cohorts A, B, C, D, E, F, G

Independently for each of these phase II trials, a Bayesian approach will be used following an adaptive trial design, allowing for smaller and more informative trials, specifically tied to decision making within a drug development program. This process allows updating knowledge gradually rather than restricting revisions in a trial design with fixed sample sizes.

In each phase II trial:

- A maximum sample size of 50 patients will be included.
- The analysis of the primary endpoint (ORR under treatment for cohorts A as well as C to G; 6-month PFR for cohort B) will be carried out sequentially, with interim analyses planned after 16-week follow-up of the first 10 patients and then every 5 patients. Inclusions will not be suspended between interim analyses, except in case of an important accrual rate in a given given trial (2 patients/center/months during at least 3 months).
- ORR (for cohorts A as well as C to G) or 6-month PFR (for cohort B) will be estimated in the eligible population assessable for efficacy (section 10.2.2). The probability of success (ORR under treatment or 6-month PFR) will be estimated from a beta-binomial model (Zohar et al., 2008). Initial parameters of the model will be pre-specified (the prior distribution represents the knowledge of the non-progression probability prior to observing the data). Successive results observed will then be used to update and refine the distribution, generating the so-called posterior distribution.
- In the absence of a strong idea about the response rates to be observed, a non-informative prior distribution (beta (1,1)) will be considered.
- Maximal response probability thresholds (based on the investigator' opinions) and minimal response probability threshold have been defined as follows:
  - Cohort A/E:  $p_0=5\%$  versus  $p_1=20\%$
  - Cohorts B/C/D/F:  $p_0=20\%$  versus  $p_1=40\%$
  - Cohorts G:  $p_0=10\%$  versus  $p_1=25\%$
- At each update of the distribution (interim analysis), a stopping rule for inefficacy will recommend stopping the trial if there is a high predictive probability ( $\geq 80\%$ ) that the ORR (for cohorts A as well as C to G) or 6-month PFR (for cohort B) is lower or equal to the minimal response probability threshold  $p_0$  defined for the cohort (Strata A and E:  $p_0=5\%$ ; Strata B/C/D/F:  $p_0=20\%$ ; Stratum G:  $p_0=10\%$ ).

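### The phase II rule for the best overall response rate, a secondary endpoint, counts only living patients, contrary to the endpoint's own definition

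*Protocol*

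**What the plan says.** Among the secondary endpoints for phase II, section 9.2.2 states: "Best overall response is defined as the best response across all time points (RECIST v1.1"). It adds: "The best overall response is determined once all the data for the patient is known". Neither sentence requires the patient to be alive at any date.

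Section 10.3.2.2 assigns each patient to one category, from confirmed complete response to inevaluable. It then gives the calculation rule. The numerator is the "number of patients alive with the best response (recorded from the start of the treatment"), and this is "divided by the number of patients eligible and assessable (section 10.2").

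The next two rules in that section also mention survival, but at a fixed time. The 6-month progression-free rate uses the "number of patients remaining alive and progression-free at 6 months from the start of the treatment", and the 6-month objective response rate uses the "number of patients alive with complete or partial response at 6 months".

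For cohorts A and C to G, section 9.2.1 defines the primary objective response rate under treatment as the "proportion of patients with objective response (confirmed or unconfirmed) under treatment based on adapted RECIST 1.1". It has no survival condition there, and none in the primary analysis rule of section 10.3.2.2.

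**The concern.** Best overall response describes what happened to the tumour. Once a response has been observed, a later death does not undo it. A rule that takes the dead out of the numerator and leaves them in the denominator measures something else: response combined with survival to an unstated date. Such a rate falls as responders die, so the same responses give different figures depending on when vital status is read.

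At stake is the descriptive reporting of a secondary endpoint. That still matters, because 11 of the 17 cohorts (A', B, and H to P) do not have the response rate under treatment as primary endpoint. For these cohorts the list in section 9.2.2 offers only best overall response and the 6-month objective response rate as response measures, and only the first covers responses at any time.

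**Working it through.** The protocol states no planned figure for best overall response, so there is none to reproduce. The check compares the texts and then illustrates the size.

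**Definition against rule.** Section 9.2.2 fixes the category from all time points, once the patient's data are complete. For a patient who dies, that is at or after death. The literal rule in section 10.3.2.2 would stop counting the patient at just that point. The two cannot both be followed.

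**Neighbouring rules.** In the two 6-month rates, *alive* is tied to 6 months and suits a landmark measure. Best overall response has no landmark, and its rule gives no date for the word.

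**Category totals.** Every assessable patient receives one category, so the category rates should sum to 100%. Under the literal rule they do not. If 10 of 50 patients had died (assumed), the counts would sum to 40, and 40/50 = 80%.

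**Size.** Inputs:

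- n = 50, from section 10.1.2 for cohorts A to G: "A maximum sample size of 50 patients will be included".
- R = 10 or 20 responders, that is 20% or 40% of 50. These match the upper response thresholds in section 10.1.2 for cohorts A and E (20%) and C, D and F (40%).
- d = share of responders who have died when vital status is read. The protocol gives no value, so d is assumed and varied.

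Formula: reported rate = R × (1 − d) / n.

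| R | d (assumed) | Counted | Rate |
|---|---|---|---|
| 10 | 0 | 10/50 | 20% |
| 10 | 0.10 | 9/50 | 18% |
| 10 | 0.20 | 8/50 | 16% |
| 10 | 0.40 | 6/50 | 12% |
| 20 | 0 | 20/50 | 40% |
| 20 | 0.10 | 18/50 | 36% |
| 20 | 0.25 | 15/50 | 30% |
| 20 | 0.50 | 10/50 | 20% |

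Exact (Clopper-Pearson) 95% limits move with the count. For 20/50 they are 26.4% to 54.8%; for 15/50, 17.9% to 44.6%; for 10/50, 10.0% to 33.7%. Without the word *alive*, the d = 0 rows apply whatever happens to the patients later.

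**Reach.** The Bayesian rules (section 10.1.2), the two-stage rules (10.1.3 to 10.1.5) and the single-stage rules (10.1.6 to 10.1.10) use the objective response rate, the progression-free rate or the disease control rate. None uses best overall response.

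**The case against.** The strongest reply is that *alive* is leftover wording. The same section places each patient in a category that does not depend on vital status and has none for death after response. The parenthesis in the rule refers to when the response was recorded, and the definition in section 9.2.2 is clear. A statistician who follows these would produce an ordinary table. The word could even mean alive when the response was recorded, which would make it harmless. Section 10.3 also requires a phase II SAP before the first phase II analysis, where this could be settled.

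Part of this stands. The harm is not certain, and carried-over wording is the likely explanation. But no passage gives the lenient meaning, and under it the word does nothing and can go. The protocol has itself written a formula that conflicts with its own endpoint definition, so this is not detail left for the SAP.

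A reader might go further and infer that responders who die before the data cut-off are certain to be dropped. The text does not support that, because the rule names no date and the cut-off is only one possible reading. A reader might also infer that the trial's response rates in general are biased. That is not supported either, because the primary objective response rate under treatment carries no survival condition.

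**Conclusion.** The point holds as a conflict between a stated calculation rule and the definition of the same secondary endpoint. Read literally, the rule lowers the best overall response rate in proportion to deaths among responders: from 20% to between 18% and 12% for 10 responders in 50, if 10% to 40% of them have died. Those shares are assumptions, and the fall occurs only if vital status is taken after the response.

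A mismatch with the objective response rate under treatment can arise in cohorts A and C to G, where that rate is the primary endpoint. It should not be claimed for all 17 cohorts: the objective response rate listed in section 9.2.2 is the 6-month landmark, which may differ from best overall response anyway. All phase II analyses are descriptive, and no primary endpoint, stopping rule, go/no-go threshold or sample size changes. It is a small error, but worth correcting.

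**What to change.** In section 10.3.2.2, delete *alive* from the best overall response rule. State that the rate for each category is the number of patients whose best response falls in that category, divided by all eligible and assessable patients, regardless of later vital status. Keep *alive* in the rules for the 6-month progression-free rate and the 6-month objective response rate.

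The cost is an edit to one rule. Data collection, design and sample size stay as they are.
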